#### Secondary Outcome Measures

Sexual function, relationship and sexual satisfaction, sexual pleasure, sexual distress, anxiety, depression, and HRQoL are secondary outcome variables in this research. A summary of the secondary outcome measures to be used in this study is presented in Table 3. Participants will not be invited to fill in all the listed measures, since secondary outcome measures will be tailored to participants’ gender, sexual orientation, and condition.

**Table 3 table3:** Secondary outcome measures.

Measure	Construct	Number of items	Dimensions	Rating scale	Cutoff points	Psychometric properties	Translation/adaptation to the target populations
Sociodemographic and clinical background questionnaires tailored to each target group	N/A^a^	11	N/A	N/A	N/A	N/A	Original version developed in Portuguese (Portugal) by the research team and translated to Dutch and German.
Mini-International Neuropsychiatric Interview (MINI) [52]	Mental disorders	16 modules (branching tree logic items)	Multidimensional	Dichotomous rating scale	N/A	Cohen k=0.7	Translated and adapted to Portuguese (Portugal), Dutch, and German.
Patient Health Questionnaire (PHQ-9) [53]	Depression	9	Unidimensional	4-point Likert scale	Mild depression (<5), moderate depression (6-10), moderately severe depression (11-15), and severe depression (>15)	α=.86	Translated and adapted to Portuguese (Portugal), Dutch, and German.
Generalized Anxiety Disorder Screener (GAD-7) [54]	Anxiety	7	Unidimensional	4-point Likert scale	Normal anxiety (<5), mild anxiety (5-9), moderate anxiety (10-15), and severe anxiety (15-21)	Primary care setting (α=.92); general population (α=.89)	Translated and adapted to Portuguese (Portugal), Dutch, and German.
World Health Organization Quality of Life: Brief Version (WHOQoL-BREF) [55]	Quality of life	26	Multidimensional	5-point Likert scale	N/A	.66<α<.84	Translated and adapted to Portuguese (Portugal), Dutch, and German.
Global Measure of Sexual Satisfaction (GMSEX) [56]	Sexual satisfaction	5	Unidimensional	7-point Likert scale	N/A	α=.94	To be translated and adapted to Dutch and German in the context of this research.
Global Measure of Relationship Satisfaction (GMREL) [56]	Relationship satisfaction	5	Unidimensional	7-point Likert scale	N/A	α=.95	To be translated and adapted to Dutch and German in the context of this research.
Sexual Pleasure Scale (SPS) [57]	Sexual pleasure	3	Unidimensional	7-point Likert scale	N/A	α=.84	To be translated and adapted to Dutch and German in the context of this research.
International Index of Erectile Function (IIEF) [58]	Sexual function	15	Multidimensional	0-5 or 1-5 numeric rating scale	≤25 expresses risk of sexual dysfunction	α>.70 for all domains	Translated and adapted to Portuguese (Portugal), Dutch, and German.
Female Sexual Function Index (FSFI) [59]	Sexual function	19	Multidimensional	0-5 or 1-5 numeric rating scale	≤26 expresses risk of sexual dysfunction	α>.9 for all domains	Translated and adapted to Portuguese (Portugal), Dutch, and German.
Sexual Distress Scale (SDS-R) [60]	Sexual distress	13	Unidimensional	5-point Likert scale	N/A	α>.85	Translated and adapted to Portuguese (Portugal), Dutch, and German.

^a^N/A: not applicable.

### Study Procedures

#### Compliance With Laws, Regulations, and Ethical Standards

The study will comply with the following laws, regulations, and ethical standards: the International Conference on Harmonisation (ICH) E6 Guideline for Good Clinical Practice (GCP), the Declaration of Helsinki (October 1996), Regulation (EU) 2016/679 of the European Parliament and of the Council of 27 April 2016 on the protection of natural persons with regard to the processing of personal data and on the free movement of such data, and repealing Directive 95/46/EC (General Data Protection Regulation), as well as the following Portuguese Decree-laws: Lei n.º 58/2019 (Assegura a execução, na ordem jurídica nacional, do Regulamento (UE) 2016/679 do Parlamento e do Conselho, de 27 de abril de 2016, relativo à proteção das pessoas singulares no que diz respeito ao tratamento de dados pessoais e à livre circulação desses dados); Lei n.º 21/2014 (Lei da Investigação Clínica), de 16 de Abril; Lei n.º 73/2015, de 27 de julho (Primeira alteração à Lei n.º 21/2014, de 16 de abril, que aprova a lei da investigação clínica, no sentido de fixar as condições em que os monitores, auditores e inspetores podem aceder ao registo dos participantes em estudos clínicos); Regulamento n.º 258/2011 (nos termos do artigo 77.º do Estatuto da Ordem dos Psicólogos Portugueses, aprovado pela Lei n.º 57/2008, de 4 de Setembro, a Ordem elabora, mantém e atualiza o Código Deontológico da Ordem dos Psicólogos Portugueses); and Linhas de Orientação para a Prestação de Serviços de Psicologia Mediados por Tecnologias da Informação e da Comunicação (TIC) da Ordem dos Psicólogos Portugueses.

In Austria, clinical psychologists will follow the Ethics Guideline from the Federal Ministry of Labour, Social Affairs, Health, and Consumer Protection. The practice of the profession of clinical psychology and health psychology in Austria is regulated by the Psychologists Act 2013, Federal Law Gazette I No. 182/2013. The Code of Professional Conduct, in the form of an ethics guideline, supplements and concretizes the professional duties laid down in the Psychologists Act 2013 and serves to safeguard and promote the professional ethics of the members of the profession. The professional and ethical principles are based on the Meta Code of Ethics of the European Federation of Psychologists’ Associations (EFPA) as follows: (1) respect for the dignity and rights of the person, (2) competence, (3) responsibility, and (4) integrity. The most recent version (as of May 21, 2021) was updated in February 2020.

The study will follow ISO standards TC314 (Ageing committees) and 82304-2 (Health and wellness apps), as noted in the AAL Guidelines for Ethics, Data Privacy, and Security, as they are also relevant.

However, due to the openness that a participatory design approach brings to research projects, fixed regulations and ethics guidelines may not suffice for Anathema. Therefore, an in-action ethics [61] approach, whereby the entire consortium is called to define the project ethos, eliciting values that the project should stand for and that should guide decisions in case the answer to ethical dilemmas falls outside normative ethics principles, is being adopted.

#### Study Initiation

The pilot feasibility trials will be initiated in February 2023. The study duration will be approximately 12 months. A study initiation visit will be performed to present the research protocol, train the local study teams, and adjust the study procedures to site specificities. A training course targeting the study psychologists will be delivered before the onset of the recruitment period to train them on Anathema’s key components, structure, and delivery, as well as on the study procedures. This course will be delivered online by certified psychologists and sex therapists.

#### Recruitment

Recruitment procedures will follow a multicenter strategy, as different consortium partners have access to different study populations. Unie KBO in the Netherlands, and Instahelp and Sigmund Freud University in Austria will be responsible for recruiting older adults. In Portugal, IPO-Porto and Europacolon will be responsible for recruiting colorectal cancer survivors. Centro de Reabilitação Profissional de Gaia will be responsible for recruiting stroke survivors in Portugal. With the support of local study team members, potential study participants will be identified by reviewing patient files at each site or following advertisements of the studies in institutional newsletters, social networks, or newspapers.

#### Consent Process

All participants will provide informed consent before any study-specific assessments and procedures are performed. Regardless of the implemented recruitment strategy, a local study team member will perform the first contact to secure the participants’ permission to be approached by the researchers. Copies of the study information sheet and informed consent forms will be provided for analysis and discussion. Subjects self-referring to participate (eg, following the study’s advertisement) will be directly contacted by the study team to provide any required clarifications before giving their consent. After informed consent is obtained, screening and baseline assessment procedures may occur.

#### Screening and Baseline Assessments

Screening and baseline assessments will be conducted by certified psychologists or psychology students supervised by the study team. The abovementioned outcome measures will be used for this purpose (Table 3). Participants fulfilling the eligibility criteria for the study will then be further assessed via a diagnostic interview. The Mini-International Neuropsychiatric Interview (MINI) [52] will structure this process. Participants with severe mental disorders will be referred to psychology departments at study sites or community mental health services.

#### Enrollment and Randomization

Participants fulfilling all eligibility criteria will be registered and randomized. Simple randomization will be performed by an independent statistician, using a computerized program. Older adults in Austria, and colorectal cancer and stroke survivors in Portugal will be submitted to subsequent simple randomization so that they are randomly assigned to one of the study psychologists. Colorectal and stroke survivors will be guided by study psychologists from SexLab, and older adults in Austria will have access to blended support provided by clinical psychologists from Instahelp. Older adults in the Netherlands will not be submitted to this second randomization procedure, given that they will get access to the self-guided version of the program. Participants randomized to Arm A (experimental condition) will receive immediate access to Anathema. Participants assigned to the WLC condition will gain access to the program approximately 8 weeks after randomization and after being submitted to a second baseline assessment to confirm their eligibility for the study.

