## Methods

### Study Design

Two-arm, parallel, open-label, waiting list, feasibility, pilot randomized controlled trials (RCTs) (Figure 1) will be conducted with older adults, stroke survivors, and colorectal cancer survivors. We will have 1 test case per target population, where different service models (unguided, guided, or blended care) will be tested. The feasibility pilot trials will be performed to identify weaknesses in the study design, test the data collection process, estimate sample sizes, and assess the feasibility of the parent RCTs. The acceptability of Anathema by study participants; the structure, format (ie, unguided, guided, and blended), and content of the study intervention; and between-group differences will also be preliminarily evaluated through this design.

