### Study Population and Research Sites

This research will target 3 study populations: older adults, colorectal cancer survivors, and stroke survivors. Older adults will be recruited in the Netherlands and Austria. Colorectal cancer survivors and stroke survivors will be recruited in Portugal. A minimum of 30 participants [38,39] per target group is expected to participate in the study trials.

The criteria presented in Textbox 1 will be used to check eligibility for participation in the study:

The study will be conducted at 5 different research sites: Unie KBO in the Netherlands; Instahelp in Austria; and IPO-Porto, Europacolon Portugal, and Centro de Reabilitação Profissional de Gaia in Portugal. Sites invited to participate were selected owing to their working standards and resources.

Eligibility criteria for Anathema’s feasibility randomized controlled trials.

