#### Study Intervention Delivery and Assessment

After randomization, participants will gain access to Anathema either via the co-developed app (older adults in the Netherlands, and colorectal cancer and stroke survivors in Portugal) or the Instahelp platform (older adults in Austria). At this stage, the 3 abovementioned service models will be tested for acceptability, feasibility, and preliminary efficacy.

The self-guided model will be tested with older adults in the Netherlands. Participants will gain access to the treatment modules every week, being prompted to complete the modules in approximately 1 week. If participants fail to complete the modules in the specified time frame, a reminder will be sent. Upon completion, participants will receive access to the following module. The preliminary efficacy of the intervention will be assessed at midtest (T2) and after the completion of the program at posttest (T3), using the measures listed above.

The guided model will be trialed by colorectal cancer and stroke survivors in Portugal. Participants will gain access to the intervention after a preliminary online or telephone appointment is conducted with their assigned study psychologist. This first e-appointment aims to discuss the program’s structure, report the baseline findings, and tailor the intervention according to participants’ needs and preferences. Once clinical psychologists and participants reach an agreement, the selected modules will be prescribed and made available weekly to the participants. Participants will be prompted to complete the modules in approximately 1 week. Within 24 hours of module completion, the study psychologists, based on the reported outcomes, will assess participants’ progress and determine whether it is appropriate or not for the participants to proceed to the next module. If so, participants will receive access to the following module. If not, study psychologists will instruct participants on what needs to be completed to advance to the next module. The preliminary efficacy of the intervention will be assessed at midtest (T2) and after the completion of the program at posttest (T3), using the measures listed above.

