The blended model will be assessed by older adults in Austria. Participants will gain access to the intervention after a preliminary 60-minute videoconference appointment is conducted with their assigned study psychologist. This first appointment aims to discuss the program’s structure and tailor the intervention according to participants’ needs and preferences. Once clinical psychologists and participants reach an agreement, the selected modules will be prescribed and made available every week to the participants. Participants will be prompted to complete the modules weekly. Within 24 hours of module completion, the study psychologists, based on the reported outcomes, will assess participants’ progress and determine whether it is appropriate or not for the participants to proceed to the next module. If so, the participants will receive access to the subsequent module. If not, clinical psychologists will instruct participants on what needs to be completed to advance to the next module. Online videoconference appointments will be conducted at the onset of the program (session 1), at week 3/4 (session 2), and at the end of the program (session 3) to blend self-care work and asynchronous support with therapeutic videoconference synchronous support. During the videoconference appointments, study psychologists will assess participants’ progress, instruct participants on how to implement treatment strategies, and determine whether it is appropriate or not for participants to proceed with the program. Upon request, sessions are also possible for participants requiring additional support from clinical psychologists. Still, they are limited to 5 extra sessions, at a maximum of 1 per week and for approximately 40 to 50 minutes. If an extra videoconference session is requested, it will replace the scheduled asynchronous session to avoid redundancy. The preliminary efficacy of the intervention will be assessed at midtest (T2) and after the completion of the program at posttest (T3), using the measures listed above (Table 3).

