#### Discontinuation of Participation

Participants may withdraw from the study at any time and for any reason, without any consequences, or be dropped from the study by the research team if a severe aggravation of baseline measures occurs. In this case, the participant will be referred to psychology services at study sites or specialized resources in the community. The main reason for withdrawal will be registered, and a final assessment will be performed whenever the participant agrees with it. Participants who are lost to follow-up may be replaced to ensure a balanced number of participants in each study arm.

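### Simple randomisation is unbiased but does not give the balanced arms the protocol wants in populations of about 30, and replacing losses cannot either; stratified blocks are a cheap improvement

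*Protocol article*

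**What the plan says.** Under Enrollment and Randomization, the protocol article fixes the method: "Simple randomization will be performed by an independent statistician, using a computerized program". No blocks or strata are named, and no allocation ratio is given.

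Under Study Population and Research Sites, the size is "A minimum of 30 participants [38,39] per target group is expected to participate in the study trials". Of the three populations, one is split: "Older adults will be recruited in the Netherlands and Austria". Study Intervention Delivery and Assessment then gives each country its own service model: "The self-guided model will be tested with older adults in the Netherlands", and "The blended model will be assessed by older adults in Austria". Colorectal cancer and stroke survivors, both in Portugal, receive the guided model.

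Under Discontinuation of Participation, the wish for balance and the means of reaching it appear together: "Participants who are lost to follow-up may be replaced to ensure a balanced number of participants in each study arm".

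The Analysis section specifies intention to treat with mixed models. The Results section reports 49 participants randomised by May 2023 and completion expected in September 2023.

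**The concern.** The protocol names balanced arms as an aim, fixes an allocation method that leaves balance to chance, and relies on replacement to restore it. This rests on what the article states, not on detail that a fuller protocol might supply.

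Arm sizes matter here because the groups are small and two of the three service models each rest on one country's older adults. Acceptability, usability, access to the program and module completion can be observed only in people who have been given Anathema. Until the waiting-list arm crosses over at about 8 weeks, that means the immediate-access arm. If chance makes that arm short in the Netherlands or Austria, few people are left to judge the self-guided or blended model.

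**Working it through.** **Inputs.** From the document: simple randomisation; two arms; at least 30 per population; older adults in two countries; 49 already randomised. Assumed: 1:1 allocation (no ratio is stated, but balanced arms are the stated aim) and about 15 older adults per country, checked from 12 to 18. The document gives no imbalance calculation to reproduce, and 30 is a cited minimum without inputs.

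**Chance of a lopsided split.** With X ~ Binomial(n, 0.5), P(smaller arm ≤ m) = 2 × P(X ≥ n − m).

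| Group size | Split | Probability |
|---|---|---|
| 30 | exactly 15:15 | 14.4% |
| 30 | 19:11 or worse | 20.0% |
| 30 | 20:10 or worse | 9.9% |
| 15 | 10:5 or worse | 30.2% |
| 15 | 11:4 or worse | 11.8% |
| 12 | 8:4 or worse | 38.8% |
| 18 | 12:6 or worse | 23.8% |

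The mean difference between arms is 4.3 people at n = 30 and 3.1 at n = 15.

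**At least one lopsided group, at one threshold (2:1 or worse).**
- Three populations of 30, with no assumption about country: 1 − (1 − 0.0987)³ = 26.8%.
- Four groups (colorectal 30, stroke 30, Netherlands 15, Austria 15): 1 − (1 − 0.0987)² × (1 − 0.3018)² = 60.4%.
- The same with countries at 12 and 18: 1 − (0.9013)² × 0.6123 × 0.7621 = 62%.

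**Short immediate-access arm.** Half of the lopsided splits go against that arm. For a country group of 15, the chance that it has 5 people or fewer is 0.3018 / 2 = 15.1%. For at least one of the two countries it is 1 − (1 − 0.1509)² = 28%.

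**Cost in precision.** The efficiency of a split a:b relative to equal arms is 4ab/(a + b)². For 20:10 or 10:5 it is 0.889 (standard error +6%); for 11:4 it is 0.782 (+13%). Averaged over simple randomisation, efficiency is (n − 1)/n: 0.967 at n = 30 and 0.933 at n = 15, an average loss of 3.3% and 6.7%.

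**What replacement can do.** Suppose a population is allocated 20:10. If nobody is lost, the rule never applies and 20:10 stands. If two are lost from the arm of 10 and both replacements enter that arm, the numbers followed are again 20:10. If replacements are simply randomised, both enter that arm with probability only 1/4; if they are placed there on purpose, they are not randomised. Those lost still count under intention to treat and in the retention measures.

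**With blocks.** In 40,000 simulated allocations per setting, blocked from the start, mixed blocks of 2 and 4 held the arm difference to at most 1 at n = 15 and 2 at n = 30. Mixed blocks of 4 and 6 held it to 3 and 2.

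**The case against.** Simple randomisation is a recognised, unbiased method. These are feasibility pilots with primary outcomes reported descriptively, and between-arm efficacy is secondary and preliminary. All of this stands. A reader might infer that the allocation method biases the comparison or makes the trials invalid; nothing in the document supports that.

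A reader might also take the 11:4 split as typical. It is a tail event (11.8% at the assumed n = 15), and the average loss is the fairer summary. The figure of 15 per country is not in the document, and 30 is a minimum; larger groups would be less affected.

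It is tempting to say that the primary outcomes as a whole are at risk. They are not: screening, enrolment, baseline completion, later questionnaire completion and withdrawals are collected before allocation or from both arms. Waiting-list participants later receive the program, which adds users.

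A further tempting claim is that condition or country becomes confounded with arm. Study Design describes separate trials with one test case per population. If allocation and analysis stay within population, condition cannot be confounded with arm; country can be imbalanced by chance only among the older adults.

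Lastly, the replacement sentence is permissive and concerns attrition. That is true, but its stated purpose is balance, which replacement cannot secure.

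**Conclusion.** The point holds as a cheap design improvement, not as an error. Simple randomisation will not reliably give the balance that the protocol asks for, and replacing losses cannot make up for it. The size is 9.9% for 20:10 or worse in a group of 30, and 30% for 2:1 or worse in a country group of 15 (39% to 24% over 12 to 18). The chance that at least one of four groups is that unbalanced is about 60%. These figures assume 1:1 allocation, and those for country groups also rest on the assumed split. The cost in precision is small on average; what matters is the chance of a very small immediate-access arm for one service model, partly offset by crossover.

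**What to change.** - For all remaining randomisations and for the parent trials, use permuted blocks of randomly varying size, centrally held and concealed from the sites. Stratify by Netherlands older adults, Austria older adults, colorectal cancer and stroke.
- Leave the 49 participants randomised by May 2023 as allocated. Against the minimum of 3 × 30 = 90, at least 41 were still to come. Document the date and reason for the change.
- Include the stratum in the mixed model wherever groups are pooled.
- Amend Discontinuation of Participation so that replacement is not used to balance arms. Any additional participant is randomised from the same list, and those lost stay in the intention-to-treat set and in the retention counts.

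The cost is one new allocation list from the independent statistician already in place, and a short amendment. The downsides are slight predictability in an open-label trial, limited by varying block sizes and central allocation, and that imbalance among those already allocated is not undone. The simulated limits on arm differences therefore apply in full only to trials blocked from the start.
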